## Statistical Analysis Plan

**Study Title:** Diabetic Retinopathy Screening Point-of-Care Artificial Intelligence – DRES-POCAI

**Clinical Trial Registration:** ClinicalTrials.gov identifier: NCT06721351

<https://clinicaltrials.gov/study/NCT06721351>

**Sponsor:** Kaiser Permanente Research Institute for the Permanente Augmented Intelligence in Medicine and Healthcare Initiative (AIM-HI). Prime award funder is The Gordon and Betty Moore Foundation.

**Intervention:** Implementation of Artificial Intelligence tool for Diabetic Retinopathy Screening at point-of-care in a primary care setting.

**Statistical Analysis Plan Version:** Version 1.1

**Statistical Analysis Plan Date:** 13 August 2024

**Purpose:** The purpose of this analysis is to evaluate the impact of a point-of-care Artificial Intelligence Diabetic Retinopathy Screening tool (EyeArt [Eyenuk, Inc, Woodland Hills, CA]), on screening completion (primary outcome) and if changes in screening completion result in a corresponding increase in diagnosis of diabetic retinopathy (secondary outcome).

### STUDY DESIGN

**Design:** DRES-POCAI is a patient-level, multi-clinic, randomized controlled, open-label, parallel superiority trial.

**Study Aims and hypothesis:** **Aim 1** of the study is to refine and operationalize a multi-component AI diabetic retinopathy screening intervention (DRES-POCAI) and implementation plan with physicians, clinical staff, and patients from Federally Qualified Health Clinics in South and Central San Diego. **Aim 2** to evaluate the impact of DRES-POCAI implementation in a primary care setting among underserved patients with diabetes mellitus on diabetic retinopathy screening completion. We hypothesize (Hypothesis 2.1) that randomization to DRES-POCAI intervention will result in an increase in diabetic retinopathy screening completion and diabetic retinopathy detection when compared to usual care; (Hypothesis 2.2) that participants receiving DRES-POCAI intervention will be more likely to (a) complete referrals to the eye specialist, (b) establish early stages of diabetic retinopathy, and (c) be less likely to present diabetic retinopathy complications due to early treatment; and (Hypothesis 2.3) that participants receiving DRES-POCAI intervention will demonstrate greater (a) knowledge, (b) attitudes, (c) self-efficacy and (d) patient satisfaction regarding diabetic retinopathy, autonomous diabetic retinopathy screening, and other diabetes mellitus-related services and resources.

**Setting:** Selected clinics from the Federally Qualified Health Center of San Ysidro Health in San Diego County, California.

**Randomization:** Participants will be randomized using a simple block randomization design to ensure equal (1:1) allocation between intervention and standard of care arms by clinic site. Randomization will be performed using a statistical program or randomizer app (<https://apps.apple.com/us/app/choice-maker-random-picker/id1387970091>).

**Blinding:** Study staff and study data analysts will be unblinded due to the intervention activities.

**Study population:** Study participants will be active SYH patients receiving medical care in one of DRES-POCAI's research clinic sites and meet the following inclusion/exclusion criteria.

#### *Inclusion Criteria*

- A diagnosis of diabetes myelitis
- Age  $\geq 22$  years
- No retinal screening during the previous 11 months
- A medical visit scheduled during the intervention period
- Ability to read and understand English or Spanish

**Exclusion Criteria**

- A prior diagnosis of diabetic retinopathy, macular edema, or retinal vascular occlusion
- Persistent visual impairment in one or both eyes
- A history of ocular injections, retinal laser treatment, or intraocular surgery (excluding cataract surgery)
- Pregnancy
- A diagnosis of mental or degenerative disease that precluded self-consent

**Outcome Measures:**

**Primary outcome**

- Completion of retinal screen (AI-DRS-System or screening by an ophthalmologist) within 3 months of enrollment and medical visit.

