**Secondary outcomes**

- Diabetic retinopathy diagnosis as determined by EyeArt or ophthalmologist
  - EyeArt-System results: normal, mtmDR, vtDR, or ungradable
  - Eye specialist referral clinical classification, using ICD-10 codes: E10.9, E11.9, E10.329, E11.329; E10.339, E11.339; E10.321, E11.321, E10.331, E11.331, E10.349, E11.349, E10.341, E11.341, E10.359, E11.359, E10.351, E11.351.
- Completion of retinal screen (AI-DRS-System or screening by an ophthalmologist) within 6 months of enrollment

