| Description of Study Intervention:                      | Study staff will generate a data query including patients with DM. A biweekly eligibility report will be generated from the electronic health record (EHR), listing patients who meet the eligibility criteria with scheduled medical appointments. Trained study staff contact potential participants (by phone or in person) and will explain the study, invite them to be part of the research study and, if they are interested, the staff will schedule a study visit to complete consent and surveys on site. Once the potential participants arrive to their study visit appointment, they will complete the consent process. During the study visit participants will be randomized into either the intervention or usual care group. A simple block randomization design will ensure equal allocations between intervention and usual care arms by clinic and assign participants to equal (1:1) allocation. For the usual care group, DR screenings with the optometrist will be scheduled according to SYHealth's protocols. The optometrist will provide the results during the visit, discuss the appropriate follow-up and document results in the medical record. For the intervention group, DR screenings will be conducted using the EyeArt® AI system (Eyenuk, Inc.) in-clinic prior to the medical visit (same day if the visit is 'in-person', or within the previous week if the medical visit is via telehealth). Results will be available in the Eyenuk web portal and can be opened directly within SYHealth's EHR. DR Screening uptake will be extracted from the EHR along with DR diagnosis, clinical, and demographic data. Increases in participant knowledge, attitudes, and self-efficacy will be collected using pre- and post- surveys. Measures will also include participant satisfaction with autonomous DR screening, and other DM-related services and resources. |

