## 4.2 SCIENTIFIC RATIONALE FOR STUDY DESIGN

The DRES-POCAI study is using a randomized controlled, open-label, parallel superiority trial. The benefit of this trial is that each participant will be randomized to two intervention options, allowing researchers to compare the relative effectiveness of multiple intervention options. The DRES-POCAI study employs a randomized controlled, open-label, parallel superiority trial design. This design is well-suited to achieve the study's aims for several reasons:

**Randomization:** Random assignment of participants to intervention and control groups minimizes confounding variables. This ensures that any observed differences in outcomes are likely due to the intervention itself and not pre-existing differences between the groups. Participants of the DRES-POCAI study will be randomized into two groups: usual care (receive a retinal screening by an optometrist) or intervention group (receive a retinal screening using a special camera and EyeArt® system, *an autonomous AI-based DR screening*). The randomization will occur after consenting and completing the surveys, prior to conducting the DR screening process (for those randomized to the intervention group).

**Open-label Design:** The open-label nature is appropriate given the practical realities of implementing a multi-component intervention with integrated technology. Blinding participants and providers to the autonomous DR screening is logistically difficult. The intervention's immediate results and potential impact on the workflow necessitate an open-label approach.

**Parallel Design:** The parallel design allows for a clear, side-by-side comparison of outcomes between the intervention and usual care groups over time. This establishes the efficacy of the multicomponent approach. Also, this approach streamlines research analysis and clearly compares outcomes within the defined study period.

**Superiority Evaluation:** The primary objective is to determine if the multi-component DRES-POCAI intervention is superior to usual care in increasing DR screenings, early detection, referrals, and patient knowledge/self-efficacy. A superiority trial directly establishes whether the intervention offers significant benefits over the current model.

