#### 4.3 JUSTIFICATION FOR DOSE

**Not applicable**

#### 4.4 END OF STUDY DEFINITION

The end of the study is defined as the completion of the last study-related activity at the close of the 2-year study. Participants of the DRES-POCAI study are considered to have completed the study if they have completed all the phases of the study, including the last scheduled DR screening shown in the **Schedule of Activities (SoA), Section 1.3**. A DRES-POCAI participant's individual study period will be considered complete upon the occurrence of the following, whichever comes latest:

**Completion of Baseline Visit:** During the first study visit, participants will complete consent, fill out a brief survey about diabetes care and eye health. At this time, the participant will also be randomized and assigned to the usual care or intervention group.

**Completion of Diabetic Retinopathy Screening:** The intervention group will complete the DR screening using a special camera and the AI system (EyeArt®), the same day of the study visit. The usual care group will complete the DR screening with an eye care provider on a different day and at a different location. The study staff will facilitate this process for participants in the usual care group by assisting them in scheduling appointments for their routine retinal screening. The study staff will provide an overview of the health education sessions, provide engagement and educational materials and schedule the follow-up health education visits with all participants. This step will ensure the completion of this important component.

**Participant Satisfaction Survey (Intervention Group Only):** Participants will complete the end-of-study satisfaction survey.

**Medical visit:** Both study groups will complete a medical visit after the screening. If the medical visit is in-person, then participants will complete it the same day as the screening. If the medical visit is via telehealth, then participants will complete it on a different day after the screening.

**Completion of Health Education Program:** Attendance at all scheduled health education sessions (3 sessions within the 6 months after the study visit) along with completion of any associated post-program evaluation surveys.

**One-Year Follow-Up Screening (Intervention Group Only):** Participants who had a negative initial DR screening will complete a follow-up screening one year after their initial enrollment and the participant satisfaction survey.

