2. **Diabetic retinopathy screening.** the screening will be conducted in a private office at each clinic study site (Chula Vista and King-Chavez) utilizing a Topcon TRC-NW400 Non-Mydriatic Retinal Camera that integrates an advanced, automated fundus camera capable of capturing true color images. It features a 360° rotating touch panel monitor, allowing the operator (staff) to capture images quickly and easily with a simple finger touch. The process also involves the EyeArt software, which is the first and only FDA-cleared AI technology capable of autonomous detection of both more than mild (mtm) and vision-threatening (vt) DR (**Appendix 3**). The EyeArt AI software will evaluate captured images to detect signs of DR within 60 seconds. Participants will receive the results as follows: normal, mtmDR, vtDR, or ungradable. The study staff will explain that the results of the screening are not the final diagnosis, and the results will be reviewed by their provider during the medical visit. The medical provider will review the results with the participant and discuss any recommended treatment plan, such as a referral to an eye specialist. Ultimately, it will be the participant's choice whether to proceed with additional tests or treatments to evaluate what was observed. The study staff will closely monitor the progress and follow up with participants with abnormal results. The results of the DR screening are also documented in participant's medical chart.

We are requesting a partial waiver of individual HIPAA authorization to review existing medical records in efforts to identify potential research subjects. The use of disclosure of PHI involves no more than minimal risk and granting the waiver will not adversely affect privacy rights and the welfare of the individuals whose records will be used. The random sample of patients from the participating clinics could not practicably be done without the waiver, as access to patient records will be necessary to provide the random sample. When potential subjects are approached to participate, they will be presented with the HIPAA research authorization (**Appendix 7**). PHI will not be re-used or disclosed for other purposes and whenever appropriate, the subjects will be provided with additional pertinent information after participation.

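### The SAP counts a retinal screen only if done by the AI system or an ophthalmologist, while the protocol has usual care screened by an optometrist or an unspecified eye care provider

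*Combined protocol and SAP*

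**What the plan says.** **SAP, Outcome Measures.** The primary outcome is "Completion of retinal screen (AI-DRS-System or screening by an ophthalmologist", to be met within three months of enrollment and the medical visit. The secondary outcomes repeat the restriction: "Completion of retinal screen (AI-DRS-System or screening by an ophthalmologist) within 6 months of enrollment", and "Diabetic retinopathy diagnosis as determined by EyeArt or ophthalmologist". Under the diagnosis outcome, however, the SAP describes the non-AI result as an eye specialist classification by ICD-10 code.

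**Protocol, who screens usual care.** The synopsis says "For the usual care group, DR screenings with the optometrist will be scheduled according to" the health center's own protocols. Sections 4.2 and 8.1 both describe "usual care (receive a retinal screening by an optometrist". Section 4.4 is looser: "The usual care group will complete the DR screening with an eye care provider on a different day and at a different location". Section 6.1.1 also says eye care provider, and the endpoint table in section 3 describes usual care as referral to the specialist.

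**Protocol, what counts.** Section 9.4.2 defines the primary endpoint as a yes/no completion of a retinal screen. The section 3 table takes completion from the EHR. Neither limits the type of provider.

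**Ungradable images.** For the AI screen, protocol 8.1 says: "Participants will receive the results as follows: normal, mtmDR, vtDR, or ungradable". Neither document says whether an ungradable result is a completed screen.

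**The concern.** The SAP names two routes to a completed screen. One is the intervention itself. The other is a provider type that the protocol does not name as the usual-care screener. If the rule is programmed as written, the control arm's standard exam fails the primary outcome while the intervention arm's exam meets it. The loss falls almost entirely on one arm and favours the intervention.

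The same wording reaches the DR diagnosis outcome. The SAP's statistical methods appear to class missing results as no diagnosis (the sentence is garbled), so retinopathy found by an optometrist could be scored as none.

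The SAP states that study staff and data analysts are unblinded. Which exams qualify should therefore be settled in writing, not left to judgement once arm-level data can be seen.

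**Working it through.** **1. The plan's own sample size.** Inputs from the SAP sample size section: 59% versus 69%, alpha 0.05 two-sided, power 80%, 1:1 allocation, Pearson chi-squared test. With the pooled-variance formula and no continuity correction:

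n per arm = [1.960·√(2·0.64·0.36) + 0.842·√(0.59·0.41 + 0.69·0.31)]² / 0.10²
= (1.330 + 0.568)² / 0.01 ≈ 360.5, rounded up to 361.

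The total is 722, which matches the SAP. Power at 361 per arm is 80.1%.

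**2. Effect of the literal wording.** Let s be the share of usual-care screens done by an optometrist. The documents give no value for s, so a range is shown. Assume that every intervention-arm completion counts and that usual-care completion by any provider is 59%.

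- Counted usual-care rate = 0.59 × (1 − s).
- Spurious difference with no true effect (59% in both arms) = 0.59 − 0.59 × (1 − s) = 0.59 × s.
- Apparent difference if the planned effect is real = 0.69 − 0.59 × (1 − s).
- Chance of a significant result favouring AI with no true effect: normal approximation, 361 per arm, nominal 2.5%.

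| s (assumed) | Counted usual-care rate | Spurious difference, no true effect | Chance of significance favouring AI, no true effect | Apparent difference if truth is 69% vs 59% |
|---|---|---|---|---|
| 10% | 53.1% | 5.9 points | 36% | 15.9 points |
| 25% | 44.25% | 14.75 points | 98% | 24.75 points |
| 50% | 29.5% | 29.5 points | >99.9% | 39.5 points |
| 100% | 0% | 59 points | >99.9% | 69 points |

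**3. Effect of correcting the wording.** Once optometrist exams count, s no longer matters. The contrast returns to 59% versus 69%, and n stays at 361 per arm.

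**4. Ungradable results.** If a fraction u of intervention completions were ungradable and none of those participants had a later eye exam inside the window, requiring a gradable result would remove 0.69 × u. With u = 10% (assumed; the documents give no rate for this setting), that is 6.9 points, leaving 62.1% versus 59%. Power at 361 per arm would then be about 13%. This is an upper bound, because protocol 2.2 plans follow-up after ungradable results and the SAP expects some of these participants to be examined by an eye specialist.

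**The case against.** The strongest reply is that nobody would apply the wording literally. Protocol 9.4.2 and the section 3 table have no provider restriction. Sections 4.4 and 6.1.1 say eye care provider. The SAP itself slips into eye specialist under the diagnosis outcome. The 59% planning rate is historical screening at the participating clinics with no provider type attached, and a control rate near zero would contradict the plan's own power calculation. All of this stands, and it makes a drafting slip the most likely explanation. It does not remove the conflict: the SAP's text on the primary outcome disagrees with the protocol, and nothing in the documents says that ophthalmologist includes optometrist.

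A reader might infer two stronger things.

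- *That no usual-care completion counts, so the effect will read as 69 points.* The documents do not support this. An ophthalmologist exam counts even on the literal reading, eye care provider could cover one, and the optometrist share is unknown. The 100% row is a limit, not an expected bias.
- *That a failed AI image is counted as a completed screen, giving a second error in favour of the intervention.* The documents are silent on how ungradable is scored. The section 3 table lists screenings completed and number of ungradable as separate items. Whether an attempted screen counts as uptake is a choice of estimand, which should be stated but is not a mistake in itself.

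**Conclusion.** The inconsistency is real, sits in the definition of the primary outcome, and should be corrected before analysis. It extends to the 6-month and DR diagnosis outcomes, though for diagnosis the SAP's own reference to an eye specialist softens it.

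The bias is conditional on the wording being applied literally, and its size depends on an optometrist share that the documents do not give. Within the illustration, even a 10% share gives a spurious difference more than half the size of the 10-point target, and a 25% share exceeds it. The direction is clear: optometrist exams are the protocol's stated screen for the control arm, so dropping them favours the intervention.

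The scoring of ungradable images is a separate and less serious gap. It calls for a stated rule and a sensitivity analysis, not a new primary definition.

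**What to change.** 1. In the SAP's primary, 6-month and DR diagnosis outcomes, replace ophthalmologist with: optometrist or ophthalmologist (eye care provider), documented in the EHR.
2. Put the same definition of a qualifying screen into protocol 9.4.2, and use one provider term for usual care in the synopsis and in sections 4.2, 4.4, 6.1.1 and 8.1.
3. As a lower-priority addition, prespecify a sensitivity analysis that scores an ungradable EyeArt result as not completed unless a gradable exam or an eye-provider exam follows inside the window. Leave the primary definition of completion otherwise unchanged.

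**Cost.** Items 1 and 2 are wording changes. The 59% and 69% rates, the 722 participants and the 80.1% power are unaffected, and the synopsis already has optometrist results entered in the medical record. Item 3 adds one analysis using counts that the section 3 table already plans to collect. Making the gradable-result rule the primary definition would not be cheap: under the 10% upper-bound example it would cut the contrast to 62.1% versus 59%.

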| Evaluate the implementation and effectiveness of a multicomponent AI clinical intervention on DR screenings, early stages of DR detection, and referrals to the specialist for follow up on abnormal results. | 
 
1. Completion of DR screening. Data will be obtained through EHR at the time of the enrollment (baseline).
 
2. Results of the DR screening: for usual care specific diagnosis; for intervention group defined as normal, mild-to-moderate DR (mtmDR), visual threatening DR (vtDR) or ungradable. Data will be obtained through EHR at the time of the enrollment (baseline) and over the duration of the study.
 
3. Referral to specialist completion status and final diagnosis. Data will be obtained through EHR over the duration of the study.
 
 | 
To evaluate the effectiveness of the clinical intervention will be tested using a RCT (Aim 2), with the “intervention group”, which is characterized by 1) conducting autonomous DR screening system (H2.1) with 2) integration of the results into the EHR (H2.2). The “usual care” group represents the existing primary care model, which involves medical visits, referral to the specialist for a DR screening, and follow-up.
 
In addition, to evaluating the impact and efficiency of the POC-AI System we will also collect AI system data, number of orders submitted, screenings completed (images), number of ungradable and time of attempts, time the patient spent in front of the camera.
 |

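### The SAP's completion outcomes count only AI or ophthalmologist screens, while the protocol has an optometrist screen the usual-care arm; read literally, this biases the primary comparison toward the intervention

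*Combined protocol and SAP*

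**What the plan says.** **SAP, Outcome Measures.** The primary outcome is "Completion of retinal screen (AI-DRS-System or screening by an ophthalmologist) within 3 months of enrollment and medical visit". One secondary outcome repeats the limit with a longer window: "Completion of retinal screen (AI-DRS-System or screening by an ophthalmologist) within 6 months of enrollment". The other is "Diabetic retinopathy diagnosis as determined by EyeArt or ophthalmologist"; the sub-bullet beneath it describes the non-AI result as an ICD-10 classification by an eye specialist.

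**Protocol, usual-care pathway.** The synopsis states: "For the usual care group, DR screenings with the optometrist will be scheduled according to SYHealth's protocols". It continues: "The optometrist will provide the results during the visit, discuss the appropriate follow-up and document results in the medical record". Section 4.2 describes the control arm as "usual care (receive a retinal screening by an optometrist", and section 8.1 (Randomization) says the same.

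**Protocol, generic terms.** Section 4.4 says "The usual care group will complete the DR screening with an eye care provider on a different day and at a different location", and section 6.1.1 also uses the generic provider term. Section 3 describes usual care as a model "which involves medical visits, referral to the specialist for a DR screening, and follow-up".

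**Protocol, primary endpoint.** Section 9.4.2 defines a yes/no variable for completing a retinal screen and does not restrict who performs it.

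No passage assigns usual-care screening to an ophthalmologist, and none says that the SAP's term covers optometrists.

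**The concern.** The SAP lists the intervention arm's planned screening method by name and omits the usual-care arm's planned method. A programmer who follows the SAP text would code a usual-care participant screened by an optometrist as not completed, although that participant did what the protocol intended. The error would lower the counted usual-care rate far more than the intervention rate, and so inflate the apparent benefit.

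Three features of the plan make an unclear rule riskier here. The SAP says that study staff and analysts are unblinded. Its data management section has the study programmer build the final analysis variables. Protocol section 6.3 relies on screening rates being an objective outcome to offset the open-label design. If the SAP wording is relaxed without a written rule, people who know the allocation could be the ones deciding which usual-care examinations count.

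**Working it through.** **1. The plan's own figure.** Inputs from the SAP sample-size section: 59% versus 69%, 80% power, Pearson chi-squared test. Two-sided 0.05 comes from that section and the significance paragraph that follows it. The mean proportion is (0.59 + 0.69)/2 = 0.64.

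n per arm = [1.960 × √(2 × 0.64 × 0.36) + 0.842 × √(0.59 × 0.41 + 0.69 × 0.31)]² / 0.10² = 360.5, rounded up to 361, or 722 in total. This matches the SAP; power at 361 per arm is 80.1%. The 59% is described as historical completion at the participating clinics, with no restriction to ophthalmologists. The power basis therefore treats ordinary usual-care screens as completions.

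**2. Model for the literal reading.** Let t be the share of usual-care completers whose screen was done by an optometrist. The documents do not give t, so it is varied. Assume true completion of 59% in both arms (no treatment effect), 361 per arm, and all intervention completions made on the AI system. Then:

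- counted usual-care rate = 0.59 × (1 − t)
- spurious gap = 0.59 × t
- true usual-care completers = 0.59 × 361 = 213

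**3. Gap needed for significance.** At t = 0.123 the counted usual-care rate is 0.517 and the mean proportion is 0.554. The critical gap is 1.96 × √(2 × 0.554 × 0.446 / 361) = 0.0725. Since 0.0725 / 0.59 = 0.123, the expected gap equals the critical value when about 12% of usual-care screens are by optometrists. The chance of significance at that point is about one half.

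**4. Chance of p<0.05 with no true effect.** For each t, this is Φ[(gap − critical gap) / √((p₁(1 − p₁) + 0.59 × 0.41) / 361)], where p₁ is the counted usual-care rate. At t = 0.10: (0.0590 − 0.0724) / 0.0369 = −0.36, giving 36%.

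| Optometrist share t | Counted usual-care rate | Spurious gap (points) | Chance of p<0.05 |
|---|---|---|---|
| 0% | 59.0% | 0 | 5% |
| 10% | 53.1% | 5.9 | 36% |
| 12.3% | 51.7% | 7.3 | 50% |
| 25% | 44.3% | 14.8 | 98% |
| 50% | 29.5% | 29.5 | about 100% |
| 100% | 0% | 59.0 | about 100% |

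Except in the first row, where the test has its nominal two-sided 5%, the chance is of a result favouring the intervention.

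**5. Check in whole participants.** Compare 213/361 in the intervention arm with 213 minus k in usual care. With k = 26, p = 0.052; with k = 27 (12.7% of 213), p = 0.043. Recoding 27 people is enough.

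**6. With the definition corrected.** Optometrist screens count, the planned comparison remains 59% versus 69%, and 722 still gives 80% power.

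**The case against.** The strongest reply is that the SAP's word is loose and nobody meant it as a scoring rule. An SAP that plans for 59% completion in usual care was not written so that planned usual-care screens score zero. Section 9.4.2 sets no provider limit, and the protocol moves between optometrist, eye care provider and specialist for the same step. Uptake is to be extracted from the EHR, where the optometrist records results, and no filter by profession is described. This stands as evidence of intent, but it does not remove the defect. The limit appears in both completion outcomes and in the diagnosis header, none of the generic terms says which professions qualify, and the text of a primary endpoint should not have to be overridden at analysis.

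Four stronger inferences are tempting, and the documents do not support them:

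- *The rule touches only usual care.* The wording applies to both arms. An intervention participant who skips the AI screen and sees an optometrist would also be scored as not completed. The effect is asymmetric, not exclusive to one arm.
- *Every AI screen counts.* The SAP lists ungradable as a possible result and does not say whether it is a completion.
- *Usual care cannot yield a retinopathy diagnosis.* The header taken alone suggests this, but the sub-bullet's eye-specialist ICD-10 classification leaves it unclear.
- *A 12% share guarantees a false positive.* It gives about an even chance.

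**Conclusion.** The mismatch between the SAP's qualifying providers and the protocol's usual-care screener is plain on the text and sits in the primary outcome. Applied literally, it biases the comparison toward the intervention. The size depends on a share the documents do not give: under equal true completion of 59% and 361 per arm, the spurious gap runs from 5.9 points at a 10% optometrist share to 14.8 points at 25%, against a planned effect of 10 points. A reader might infer that usual care will be scored 0 of 361 and superiority declared on provider type alone. That outcome needs both the literal rule and 100% optometrist screening; it is a bound, not a forecast, and probably not what the authors intended. The diagnosis outcome has the same wording problem in a less clear-cut form.

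**What to change.** In the SAP's primary outcome and in both secondary outcomes, replace the word ophthalmologist with *eye-care provider (optometrist or ophthalmologist)*, and state that the rule applies identically in both arms. The SAP then agrees with the protocol's usual-care pathway and with the provider-neutral endpoint in section 9.4.2, which can stay as it is. The cost is three lines of SAP wording, best changed before any outcome variable is derived. Sample size and data collection are unaffected.
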